## Abstract

**Introduction:**

Hearing loss is highly prevalent and impacts many aspects of a person’s life, including communication, social engagement, employment, general health and well-being. Yet, many people do not access hearing healthcare and are unaware of the range of hearing healthcare options available. Barriers to hearing healthcare include poor understanding of hearing loss and its impact; poor knowledge of help-seeking for hearing healthcare options; minimal support to help decide which option is best; and stigma related to hearing loss. These barriers lead to many people not receiving the hearing healthcare they need. Guided by theories of behaviour change and implementation science, *HearChoice*, an online tailored decision support intervention, has been co-developed to empower adults with hearing difficulties by offering them choice and control over their own hearing healthcare. *HearChoice* aims to facilitate informed decisions, accessibility and uptake of hearing healthcare, including a wide range of interventions, for adults with hearing difficulties. The objectives of the trial are to evaluate the effectiveness, health economics and feasibility of *HearChoice*.

**Methods and analysis:**

This online randomised controlled trial will recruit participants with hearing difficulties across Australia, with an anticipated sample size of 640. Participants will be randomised to either *HearChoice* (treatment) or an Australia-specific Hearing Option Grid (active control), both delivered online. Outcomes will be assessed at baseline when the interventions will be offered, at 7 days post-intervention (primary endpoint) and at 3 months post-intervention. An email reminder will be sent at 1-month post-intervention. The primary outcome is decisional conflict. Secondary outcomes include measures of readiness and self-efficacy to take action, hearing-related quality of life and empowerment, assessment of the value and impact of *HearChoice*, work performance and health, and feasibility measures. Primary analysis will compare outcomes between *HearChoice* and the active control at the primary endpoint.

**Ethics and dissemination:**

The study was approved by the Curtin University Human Ethics Committee (HRE2023-0024). All participants will provide written informed consent prior to participation. A broad dissemination plan of the study findings includes peer-reviewed publications, scientific conference presentations, articles and presentations for the wider community and public written in lay and accessible language, and social media.

**Trial registration number:**

Australian New Zealand Clinical Trials Registry (ACTRN12624001139561).

STRENGTHS AND LIMITATIONS OF THIS STUDYThe online nature of the randomised controlled trial (RCT) will enable Australia-wide participation and access to a large number of people.The online, rather than clinic-based, approach is more likely to recruit those at the early stages of their hearing journey.The RCT will evaluate both the effectiveness and health economics of decision aids for hearing difficulties.The online nature of the RCT and intervention may not be accessible to all demographic groups and may not be representative of the general population.Participants will not be clinically diagnosed with hearing loss (ie, using pure-tone audiometry) as part of the study.

## Introduction

### Background and rationale

 One in seven Australian adults has hearing loss (approximately 3.95 million), which is estimated to increase to 7.78 million by 2066.^1^ The negative impacts of hearing loss are pervasive, impacting communication, interaction with others and social engagement, leading to overall poorer health and well-being,^2^ as well as reduced employment, income, advancement and well-being in the workplace.^3^ Additionally, hearing loss in midlife is a primary potentially modifiable risk factor for dementia.^4^ Despite hearing aids being clinically effective,^5^ only one in three people who would benefit from hearing aids have them.^6 7^ There is a significant time delay of 8.9 years, on average, from becoming aware of hearing difficulties to obtaining hearing aids.^8^ Additionally, the majority of working-aged adults aged between 26 and 64 years, and many who are retired, are not eligible for fully or partially subsidised hearing healthcare through the Australian Hearing Services Programme (HSP). These barriers and low uptake of hearing healthcare contribute to the economic cost of untreated hearing loss to the Australian economy reported at $A 41 billion in 2019–2020.^1^

Low uptake of hearing healthcare is common, with many people not seeking help for hearing problems.^9^ This issue was highlighted by the HSP review published in 2021 that found 60% of those eligible for the HSP do not engage with it.^10^ Understanding the reasons for low uptake of hearing healthcare early in the hearing journey is important to reduce the burden of untreated hearing loss in Australia. The HSP review reported barriers including poor understanding of the impacts of hearing loss, inappropriate expectations about hearing aids, and a lack of information, or misinformation, about hearing loss, hearing aids and other rehabilitation options. For example, a large proportion of people do not believe hearing aids provide benefits.^10^

Part of this lack of understanding may arise from there being little information offered about alternative options available (eg, range and function) for hearing loss, beyond commonly prescribed hearing aids.^11^ Alternative options include technological or non-technological options, for example, over-the-counter self-fitting hearing devices and ‘hearables’,^12^,^14^ assistive listening devices,^15^ communication training,^16^ educational support^17 18^ and auditory-cognitive training.^19^ In addition to the lack of information about the options, client preferences are often not explored, and there is limited information about available hearing healthcare pathways, how to access them and the available options.^20 21^ Lack of information coupled with minimal consideration of personal preferences reduces people’s capacity for informed decision-making, limiting their choice and control over their personal hearing healthcare.^21^ This can lead to reduced help-seeking and action, which is seen in a substantial proportion of those who seek help initially but do not subsequently follow through with decision-making.^22^

Helping a person make informed decisions is a central tenet of audiological practice and person-centred care more generally.^23^ To promote decision-making and help-seeking behaviours, it is necessary to increase capability (eg, recognising hearing difficulties, knowing where to go for help), opportunity (eg, support in decision-making and having access to good-quality information) and motivation (eg, understanding the importance of managing hearing loss).^9^ As such, the research is underpinned by the COM-B model, a framework for understanding behaviour change that proposes behaviour (B) involves three key factors: capability (C), opportunity (O) and motivation (M).^24^ More recently, a comprehensive framework of barriers and enablers to help-seeking and informed decision-making based on the COM-B model has been developed as part of the *HearChoice* research.^21^

Informed decision-making has six key elements: situation diagnosis, choice awareness, option clarification, discussion of harms and benefits, deliberation over patient preferences and making the decision,^25^ all required by the International Patient Decision Aid Standards (IPDAS; http://www.ipdas.ohri.ca/). Decision aids have a positive impact in general healthcare by improving knowledge, informed choice and decision-making.^25 26^ The development of patient decision aids has been highlighted as a research priority in the Australian HSP review^10^ and Roadmap for Hearing Healthcare^27^ and the UK NICE Guidelines for Hearing Loss.^28^ However, evidence-based co-designed decision aids based on IPDAS criteria are limited.^29^

Supporting patients in decision-making through education, and promoting client readiness and motivation in their hearing healthcare, is likely to reduce the delay between awareness of hearing difficulty and seeking help.^10^
*HearChoice*, a newly developed online, modular, interactive and individualised decision support intervention, seeks to tailor this support to close the gap and reduce the identified barriers to hearing healthcare.^21^

### Objectives

This randomised controlled trial (RCT) aims to:

Evaluate the effectiveness of the *HearChoice* intervention, as compared against a hearing health option grid, in terms of improving decisional conflict (primary outcome), and a range of secondary outcomes.Perform an economic analysis of *HearChoice* in adults seeking help for their hearing loss.Assess the acceptability and feasibility of *HearChoice* in facilitating decision-making in the target population.

## Methods and analysis

### Trial design and setting

This is a two-arm superiority parallel RCT with an active control. The trial will compare the *HearChoice* decision support intervention to a modified Hearing Loss Option Grid originally developed in the UK based on a qualitative study^20^ and adapted for use in Australia (online supplemental appendix 1).

This article outlines the protocol (V.1.0, 20.2.25) of the *HearChoice* (RCT), which meets the Standard Protocol Items: Recommendations for Intervention Trials (SPIRIT) guidelines.^30^ The SPIRIT Checklist is shown in online supplemental file 2.

The trial was prospectively registered with the Australian New Zealand Clinical Trials Registry. This registration includes all items from the WHO Registration Data Set (V.1.3.1).^31^

The online trial will be conducted by the Behavioural Insights Team (BIT) on Predictiv, their online experiment platform. Participants will be recruited through Pureprofile, a global research panel, who will recruit participants across Australia and send them a link to the trial. All aspects of the trial (eg, informed consent, decision tool interventions and measures) will be delivered online. Participants in both arms will follow the same study schedule, with outcome measures at baseline (T0), 7 days post-intervention (T1, primary endpoint) and 3 months post-intervention (T2) (see figure 1). Participants will be paid participation fees by Pureprofile for completing each of the T0, T1 and T2 surveys. Participants will be paid the same regardless of the intervention arm to which they are allocated. The study sponsor is Curtin University, Perth, Australia, who is responsible for the conduct of the study.

**Figure 1 F1:**
[figure not shown]
Flow diagram of enrolment, interventions and measures.

### Participants

#### Eligibility criteria

The inclusion criteria are: (1) aged 26 years and older, (2) subjective experience of hearing difficulty, (3) currently residing in Australia, (4) regular access to a computer, tablet or smartphone to navigate websites and (5) a good understanding of English. The exclusion criterion is current users of hearing aid(s).

#### Sample size

We aim to recruit a sample of 640 participants at randomisation. This sample size is based on a required sample of 352 at T1 and a rate of 45% attrition between T0 and T1. This rate of attrition is typical for studies completed using the Predictiv platform.

The required sample size at T1 was calculated as necessary to detect a moderate effect size of 0.3 at 80% power and an alpha level of 0.05 in a two-tailed test. This moderate effect size was selected pragmatically as there are no published RCTs of decision aids for hearing interventions. Review of previous RCTs of patient decision aids for other, mainly chronic, conditions using the Decisional Conflict Scale revealed a wide range of reported effect sizes (0.03–3.94).^32 33^ The selected effect size of 0.3 is slightly smaller than that reported in a previous study of a similar online decision aid.^34^

### Interventions

#### Treatment group: HearChoice programme

*HearChoice* is a web-based app that has been co-designed through an iterative, participatory approach, based on design thinking principles, with adults living with hearing loss, advocacy groups and hearing care professionals (HCPs).^21^
*HearChoice* is an interactive patient decision-support intervention for adults with hearing difficulties comprising six sections (About, Learn, Services, Choice, My Plan, Resources). Participants will independently access *HearChoice* via their smartphone, tablet or computer by following a link via a unique identifier number. *HearChoice* is designed to provide a step-by-step guide to decision-making about hearing healthcare, including background information about hearing loss, the importance of management, and guidance about hearing healthcare options. *HearChoice* is presented using written text, images, self-report questionnaires, an online hearing test, videos of personal experiences of adults with hearing difficulties, and a set of relevant resources (eg, technology levels and costs for hearing aids and direct-to-consumer products, implantable devices, tinnitus). Information is presented via expandable boxes grouped under sub-headings (figure 2). Participants can choose where to go and what to engage with, although it is recommended that they follow the flow through the sections from About to My Plan, where they make their decision. The six sections are:

**Figure 2 F2:**
[figure not shown]
Exemplar screenshots of HearChoice. (**a**) Information delivered via expandable boxes (Learn, Services) and (**b**) taking action for a preferred option (My Plan).

*About*. Explains what *HearChoice* is, its aim and how to use it.*Learn*. Three subsections on evidence-based information on hearing loss and management: understanding hearing loss; impact of hearing loss and benefits of hearing healthcare; ‘Mythbusters’ to dispel the myths about hearing loss and management.*Services*. Four subsections about the Australian hearing healthcare provision: questionnaire to assess eligibility for Australian government support; healthcare professionals and services; hearing tests, including screening and speech understanding; an online digit triplet test in noise hearing test, and the 5-item Social Isolation Measure to assess psychosocial aspects of hearing loss.^35^*Choose*. Three subsections offer a broad range of 11 hearing healthcare options: values clarification questionnaire (what matters most for you to hear well?); non-device options comprise five person-centred options including ‘Do Nothing’; technology options comprise six options including ear-level and remote hearing devices. For each option, provision and costs are described. Participants can choose the preferred options that will meet their needs, which are added to their My Plan.*My Plan*. Using an interactive format, participants can compare their chosen options and obtain more in-depth information about options, including pros and cons. Participants are prompted to decide whether to take action or not. Potential actions, such as seeing an HCP or accessing an online programme, are presented which they can select, along with selecting a date by which to complete the action. The ‘My Plan’ page is built, providing a tailored description of hearing choice options that suit their preferences and values. This can be saved or printed for future reference (eg, to take to an appointment with an HCP).*Resources*. A list of 14 sets of resources about hearing healthcare (eg, medical advice; understanding hearing aid technologies, including costs and technology levels; hearing market), special populations and conditions (eg, hearing loss and dementia; tinnitus; cochlear implants) and information About *HearChoice*.

*HearChoice* adheres to the IPDAS guidelines,^36^ meeting all six qualifying criteria confirming that *HearChoice* is a valid decision aid tool. All 10 IPDAS Certification criteria are met, indicating a high-quality and evidence-based decision aid and suggesting trustworthiness, usability and effectiveness in informed-decision-making relating to hearing health. The development of *HearChoice* was underpinned by behaviour change theory^24^ and implementation science,^37^ addressing barriers and enablers to help-seeking and decision-making.^21^

#### Active control Group: Option Grid

A Hearing Loss Option Grid (a one-page PDF) that met IPDAS guidelines^36^ was developed for the Australian hearing healthcare system, based on an existing Option Grid developed in the UK (online supplemental appendix 1). The Option Grid was designed to provide a framework for decision-making about technology-based hearing management options, presented using written text. The option grid included three options (hearing aids, assistive listening devices and do nothing), and information for each option about what this involves, expectations, benefits, cost and extra considerations such as maintenance.

#### Criteria for discontinuing or modifying allocated interventions

There are no a priori criteria for discontinuing or modifying allocated interventions. Participants will be informed that they are able to withdraw participation at any point in the study without negative consequences for their hearing healthcare. They do not have to give a reason for withdrawal.

#### Strategies to improve adherence to interventions

Participants can access their allocated intervention throughout the 3-month period of the trial by either bookmarking (*HearChoice*) or downloading (Option Grid) the intervention. Clear information will be presented to explain how this can be achieved. The 7-day period between allocation of the intervention (T0) and the primary endpoint (T1) will allow participants time to work through the content at their own pace and spend as little or as long as they choose. At T1 and T2 timeframes, the intervention will be offered again within the survey, with the option to bookmark or save. Similarly, the intervention will be re-presented at the 1-month timepoint in an email sent to nudge the participant that also asks them to think about their options, what actions they have taken and what actions they intend to take.

#### Relevant concomitant care permitted or prohibited during the trial

There will be no restrictions regarding concomitant care during the trial outside of the trial arms. Similarly, there will be no restriction on using other hearing-related websites, although participants will be asked to report whether they did so. Information regarding any action taken towards seeking hearing healthcare will be obtained at all follow-up data collection points (T1, 1m, T2).

#### Provisions for post-trial care

Participants in the *HearChoice* group will be receiving the best available evidence of a broad range of options available for dealing with hearing difficulties. Those allocated to the active control group will be offered access to the *HearChoice* website at the conclusion of the 3-month follow-up period.

### Outcomes

Delivery of primary and secondary outcomes via an online survey is shown in table 1. Participants will be allowed to complete the survey up to 7 days following its delivery at T0, and 10 days for T1, 1m and T2. All questions, if applicable, are mandatory to enable progression through the survey. Reminders will be sent to facilitate survey completion: for T0, one reminder 2 days following initial survey delivery, and for T1 and T2, reminders at 2 days and 7 days following initial surveys.

**Table 1 T1:** Summary of outcomes, instruments and timepoint for administration at baseline (T0), 7 days post-intervention (T1) and 3 months post-intervention (T2)

Outcome	Instrument	Baseline (T0)	7 days (T1)	3 months (T2)
	**Effectiveness outcomes**			
Primary outcome				
Decisional conflict	Decisional conflict Scale	X	X	X
Secondary outcomes				
Readiness for hearing healthcare	Ida Institute Line 1	X	X	X
Self-efficacy for hearing healthcare	Ida Institute Line 2	X	X	X
Hearing-related quality of life	Revised Hearing Handicap Inventory—Screening	X		X
Empowerment	Empowerment Audiology Questionnaire—15 items	X	X	X
Intention to take action	Bespoke project-related question		X	X
Preparedness for decision-making	Preparation for Decision-making Scale		X	X
Impact of the decision tool	User-Mobile Application Scale—User		X	X
Action taken	Bespoke project-related question		X	X
Benefit of hearing aids	Glasgow Hearing Aid Benefit Profile Part 2			X
Economic benefit	WHO Health and Work Performance Questionnaire	X		X
	**Feasibility and implementation**			
Acceptability	Acceptability, usability, usefulness, satisfaction, accessibility		X	X
Consent rate	Completion at T0 vs number of those eligible	X		
Attrition	Completion at T1 vs T0	X	X	
Adoption	Uptake of intervention (treatment and control)	X	X	X
Fidelity (adherence)	Website analytics (throughout study)	X	X	X

To ensure high quality data, participants will be asked to complete an attention check at all time points prior to the outcome measures. The attention check is to identify whether participants can read and respond correctly to a simple instruction to minimise compromising data quality. Participants will be asked to indicate that they have read ‘Moderately interested’ and ‘Slightly interested’ in a sentence. Participants who fail the check at T0 will be excluded from the trial. Participants who fail at the other time points will be able to continue with the survey, but their failure of the attention check will be noted and potential impacts will be evaluated in the analysis.

#### Primary outcome

The primary outcome, decisional conflict, is measured by the 16-item Decisional Conflict Scale.^38^ Decisional conflict is the uncertainty a person experiences when faced with a choice that involves risk, loss, regret or challenges to personal values. In this study, the choice relates to hearing healthcare. There are five subscales (Informed, Values Clarity, Support, Uncertainty, Effective Decision).

The *HearChoice* intervention will be considered effective if the estimated effect on this outcome is considered statistically significant (p<0.05) and clinically significant (Cohen’s *d*=moderate (0.3) or greater) for the overall score.

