### Assignment of interventions

#### Sequence generation

Simple randomisation will be used, with the aim of obtaining a ratio close to 1:1. With large sample sizes, simple randomisation should allow us to reach the same allocation as other, more complex methods, such as block randomisation. Participants will be assigned a random number (1 or 2), corresponding to the relevant trial arm. This will be done on the Predictiv platform when participants enter at T0. The randomisation uses a sequence of pseudo-random numbers generated using a Mersenne Twister Random Number Generator, and the numbers are automatically stored in the data on Predictiv. There will be no restrictions (eg, blocking) on the randomisation.

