#### Statistical methods

A full statistical analysis plan will be finalised prior to data lock. No interim analyses to stop for efficacy or futility are planned.

Demographic and hearing characteristics of the intervention and control groups will be described at T0. For the primary and secondary outcome measures at each timepoint (T0, T1, T2), we will provide the mean and 95% CIs by group. Differences between groups will be explored at each timepoint using independent samples t-tests, with correction for Type I errors as required. The primary analysis will evaluate whether there is a difference between the intervention and control groups at the primary study endpoint T1.

Analysis of variance will be used to compare change over time on each outcome measure between the intervention and control groups. Additional analyses will be performed to explore the impact of demographic, hearing-related characteristics and intervention engagement on the outcome measures over time between groups.

Economic analysis involves estimation of societal costs and costs associated with the development and use of the decision aid, and costs of fitting hearing aids or equivalent. Additionally, the impact of the intervention of work will be explored on both employment status (focusing on hours of work per week), and measures of absenteeism and presenteeism, specifically the WHO Health and Performance Questionnaire.^42^

Acceptability and feasibility data will be summarised by descriptive statistics and compared within and between intervention groups. This will include a flow diagram of the numbers of participants across the trial as indicated in figure 1 (eg, number screened, eligible, completion at each timepoint). For the *HearChoice* group, additional analyses using website analytics on participants’ engagement with *HearChoice* across the trial period will be performed based on content viewed. These results, along with those from the evaluation outcome measures, will help inform future trials of decision aids in hearing healthcare.

After completion of all planned analyses, data will be made available on reasonable request and on signing a unilateral data sharing agreement.

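### The 80% power belongs to the significance test; the declared effectiveness rule, which also needs an estimated d of at least 0.3, has about a 50% chance of being met at the planning effect

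*Protocol article*

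**What the plan says.** The Primary outcome section of the Protocol article sets the rule for the trial's main conclusion. HearChoice "will be considered effective if the estimated effect on this outcome is considered statistically significant (p<0.05) and clinically significant", and clinical significance is defined as a Cohen's d that is "moderate (0.3) or greater) for the overall score" of the Decisional Conflict Scale. The two conditions are joined by 'and', and both apply to the estimated effect.

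The Sample size section gives the T1 requirement as the number "necessary to detect a moderate effect size of 0.3 at 80% power and an alpha level of 0.05 in a two-tailed test". Recruitment then follows from "a required sample of 352 at T1 and a rate of 45% attrition between T0 and T1", which leads to 640 randomised.

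The Statistical methods section names independent samples t-tests for the group comparisons and places the primary comparison at T1. Under Sequence generation, allocation is by simple randomisation, aiming at roughly equal arms.

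**The concern.** The sample size calculation deals with one event, p<0.05. The effectiveness rule requires two, p<0.05 and an estimated d of at least 0.3. The true effect assumed for planning is also the value that the estimate must reach. An essentially unbiased estimate of a true 0.3 falls below 0.3 about half the time, whatever its precision.

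The primary conclusion is at stake. A reader who sees 80% power in one section and the effectiveness rule in another will naturally take 80% as the chance of a positive conclusion if the true effect is 0.3. The document gives no figure for that chance. Results with an observed d between about 0.21 and 0.30 would be statistically significant and yet, by the trial's own rule, would not count as effective. If this is noticed only once results are known, any clarification will look like a change of criterion.

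**Working it through.** **Inputs.** From Sample size: d = 0.3, power 80%, two-sided alpha 0.05, 352 at T1, 45% attrition, 640 randomised. From Primary outcome: p<0.05 and estimated d ≥ 0.3. From Statistical methods: independent samples t-test. From Sequence generation: arms close to 1:1, taken here as 176 per arm, so df = 350.

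**1. The plan's own figure.** The exact two-sample t-test at d = 0.3, 80% power and two-sided alpha 0.05 needs 175.4 per arm, rounded up to 176, or 352 in total. Power at 176 per arm is 80.1%. Allowing for attrition, 352 / (1 − 0.45) = 640. Both stated numbers are reproduced.

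**2. Which limb decides.** The smallest significant observed d is

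t(0.975, 350) × √(2/176) = 1.967 × 0.1066 = 0.210.

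An observed d of exactly 0.30 corresponds to t = 0.3 × √(176/2) = 2.81, or p = 0.005. Any estimate that meets d ≥ 0.3 is therefore already significant. The p-value limb is redundant from a total of 174 at T1 upwards.

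**3. Probability of meeting the full rule.** This is P(T ≥ 0.3 × √(n/2)), where T is noncentral t with 2n − 2 degrees of freedom and noncentrality d × √(n/2). With n = 176 per arm:

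| True d | p<0.05 alone | p<0.05 and estimated d ≥ 0.3 |
|---|---|---|
| 0.25 | 64.8% | 32.1% |
| 0.30 | 80.1% | 50.1% |
| 0.35 | 90.6% | 68.0% |
| 0.39 | 95.4% | 80.0% |
| 0.40 | 96.3% | 82.5% |

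A simulation of 100,000 trials at true d = 0.3 gave 80.0% for significance alone and 49.9% for the full rule. Hedges' small-sample correction gives 49.8%.

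**4. True effect needed for 80%.** Solving the noncentral t gives d = 0.390. The normal approximation agrees: 0.3 + 0.8416 × 0.1066 = 0.390.

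**5. Effect of a larger sample at true d = 0.3.** The full rule is met with probability 50.1% at 320 per arm (all 640 analysed) and 50.0% at 1000 per arm. Power for p<0.05 alone at 320 per arm would be 96.6%. Better retention therefore helps the test but not the rule. Baseline adjustment would act in the same way.

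**6. False-positive side.** With no true effect, the chance of meeting the rule in HearChoice's favour is 0.26%, against 2.5% for the significance test in that direction.

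**The case against.** The strongest reply is that the Sample size section claims only what it delivers. It speaks of detecting an effect of 0.3 in a two-tailed test, and for that test 80% is right. A reader might infer that the power was miscalculated, or that the true power is 50%. The document does not support that: it never attaches the 80% to the effectiveness rule, and the arithmetic reproduces. This part of the reply stands, and the point is limited to the mismatch between what was powered and what will be declared.

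A second reply is that 0.3 may be the smallest worthwhile effect and not the expected one. The section says that it was chosen pragmatically and lies slightly below the effect seen with a similar online aid. About 50% at the threshold is a property of any rule based on a point estimate. This also stands in part. But the earlier effect size is not given, and even at a true d of 0.35 the probability is only 68%. Nothing in the document claims a true effect near 0.39.

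Third, requiring clinical as well as statistical significance is a legitimate choice, and withholding the label 'effective' from a significant d of 0.21 to 0.30 is exactly what the second limb is for. That is accepted. A reader might also suspect that the rule favours the sponsor or inflates type I error. It does the opposite, and the estimate and its interval remain reportable whatever the label.

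The matter cannot simply be left to the statistical analysis plan. The rule and the power statement are both fixed in this document, and an analysis plan consistent with them would inherit the gap.

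**Conclusion.** The point holds as a mismatch between two stated elements, not as an error in the sample size. The 352 at T1 give 80.1% power for the t-test at a true d of 0.3. The declared rule is stricter, and at the planned size it reduces to an observed d of at least 0.3. At a true d of 0.3 it is met with probability of about 50%, so in roughly 30% of trials (80.1% − 50.1%) the result would be significant but not declared effective. An 80% chance of meeting the rule needs a true d of about 0.39.

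The figures assume equal arms of 176 at T1, an unadjusted t-test, d standardised by the pooled SD, and the threshold applied to the point estimate, which is how the Primary outcome section words it. Had the rule meant a confidence limit at or above 0.3, the probability would be far lower, but the text does not say that. Actual T1 numbers may differ from 352. At a true d of 0.3 this barely moves the 50%, so long as at least 174 are analysed.

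**What to change.** Keep the two-part rule and restate the Sample size section. Label the 80% as power for the two-sided t-test at a true d of 0.3. Add that, with 352 at T1, the probability of meeting the effectiveness criterion is about 50% at a true d of 0.3 and 80% at a true d of about 0.39. Carry the same statement into the statistical analysis plan, which the protocol says will be finalised before data lock.

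Alternatively, if the sponsor prefers, rest the effectiveness claim on p<0.05 in favour of HearChoice, and report d with its 95% CI against 0.3 as the interpretation of clinical relevance. This lowers a prespecified bar, so it must be settled and documented before any outcome data are seen.

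The cost is wording only, with no extra participants. Under the first option, the figure given for the trial's declared criterion becomes less favourable.
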